# Caring Near and Far by Connecting Community-Based Clients and Family Member/Friend Caregivers Using Passive Remote Monitoring: Protocol for a Pragmatic Randomized Controlled Trial

**DOI:** 10.2196/15027

**Published:** 2020-01-10

**Keywords:** home care, family caregiver, friend caregiver, remote sensor, older adults, caregiver burden

## Abstract

**Background:**

Significant chronic disease challenges exist among older adults. However, most older adults want to remain at home even if their health conditions challenge their ability to live independently. Yet publicly funded home care resources are scarce, private home care is expensive, and family/friend caregivers have limited capacity. Many older adults with chronic illness would require institutional care without the support from family member/friend caregivers. This role raises the risk of physical health problems, stress, burnout, and depression. Passive remote monitoring (RM), the use of sensors that do not require any action by the individual for the system to work, may increase the older adult’s ability to live independently while also providing support and peace of mind to both the client and the family member/friend caregiver.

**Objective:**

This paper presents the protocol of a study conducted in two provinces in Canada to investigate the impact of RM along with usual home care (the intervention) versus usual home care alone (control) on older adults with complex care. The primary outcome for this study is the occurrence of and time to events such as trips to emergency, short-term admission to the hospital, terminal admission to the hospital awaiting admission to long-term care, and direct admission to long-term care. The secondary outcomes for this study are (1) health care costs, (2) client functional status and quality of life in the home, (3) family/friend caregiver stress, and (4) family/friend caregiver functional health status.

**Methods:**

The design for this study is an unblinded pragmatic randomized controlled trial (PRCT) with two parallel arms in two geographic strata (Ontario and Nova Scotia). Quantitative and qualitative methodologies will be used to address the study objectives. This PRCT is conceptually informed by the principles of client-centered care and viewing the family as the client and aims at providing supported self-management.

**Results:**

This study is supported by the Canadian Institutes for Health Research. A primary completion date is anticipated in fall 2022.

**Conclusions:**

Findings from this real-world rigorous randomized trial will support Canadian decision-makers, providers, and clients and their caregivers in assessing the health, well-being, and economic benefits and the social and technological challenges of integrating RM technologies to support older adults to stay in their home, including evaluating the impact on the burden of care experienced by family/friend caregivers. With an aging population, this technology may reduce institutionalization and promote safe and independent living for the elderly as long as possible.

**Trial Registration:**

International Standard Randomised Controlled Trial Number (ISRCTN) 79884651; http://www.isrctn.com/ISRCTN79884651

**International Registered Report Identifier (IRRID):**

DERR1-10.2196/15027

## Introduction

Older adult Canadians (aged 65 years and older) experience significant chronic disease challenges [1], yet most older adults want to remain at home even if their health conditions challenge their ability to live independently [2].

There is evidence that “...when home care is appropriately managed and properly integrated into the health care system, it can improve the health and well-being of many seniors and their families and reduce the costs of care in hospitals and long-term care facilities” [3]. However, evidence suggests that there is room for improvement in current home care service delivery. Recent studies showed that 25% of Canadian older adults receive only partial home care services and experience unmet home care needs that create a cascade of events resulting in deterioration of older adults’ health and the need for institutionalized care [2,4]. Older adults want to be assured that their health care needs can and will be effectively addressed [5].

Part of the challenge in caring for older adults in their homes lies in providing suitable home care services and ensuring that older adults can safely follow their established treatment plan (eg, adherence to medication protocol). From a health care perspective, we have yet to feel the full effects of the impact of older adult health care challenges [6]. The transfer of health care services to the home setting is a strategic move intended to accommodate the desire of many older adults to remain at home and minimize acute care costs [7]. Yet home care resources are tenuous due, in part, to challenges in attracting and sustaining a work force (eg, nurses) that will be paid lower wages than in the hospital sector [3,5].

Deficiencies in availability of publicly funded home care means that family/friend caregivers are increasingly called on to play a larger role in the care of older adults within the home setting [3]. As the care needs of older adults increases, the average number of hours of care provided by family/friend caregivers increases significantly in contrast to the limited publicly funded home care service provision [3]. There is growing recognition that the majority of older adults would not be able to stay in their homes without the support from family/friend caregivers [5,8]. Family/friend caregivers in Canada are providing unpaid care to approximately 97% of home care recipients [8]. A Statistics Canada report indicated that in 2012 family/friend caregiving was provided by more than 8 million Canadians [9] at a conservative cost estimate of $25 billion (US $19 billion) in health care service [10]. These spouses, adult children, friends, and neighbors [8] provide transportation; prepare meals; clean and maintain the home; schedule and coordinate appointments; advocate for care services; manage finances; help with medical treatment; and provide emotional support and personal care such as bathing, feeding, and toileting [11]. The presence (physically or virtually) of family/friend caregivers is key to whether or not older adults with complex care needs can remain in their own home [3,12]. Yet for the family/friend caregiver, this role creates increased risk of physical health problems, stress, burnout, and depression [12].

Family/friend caregiver stress constitutes a depletion of personal resources and is reflected by family/friend caregivers’ distress, anger, or depression as a consequence of an accumulation of tasks and responsibilities that impacts their sense of independence and freedom [13]. A study by Duxbury et al [6] of employed family caregivers (eg, spouse, adult child) in Canada found that the average caregiver maintained their supportive role for about 5 years; many taking on the role because they cared deeply about their family member. However, approximately 40% of family/friend caregivers reported that they assumed the caregiver role by default; there was no one else to take on the responsibility for care. There are significant costs to Canadian family/friend caregivers of an elderly family member related to altered work patterns, loss of career advancement, and increased use of Canada’s health care system [6,8,14]. Family/friend caregivers are also at risk of financial strain associated with poorer physical and mental health, greater work-life conflict, increased workplace absenteeism, lower job satisfaction, and a higher number of visits to the emergency room and hospital. Fast et al [14] estimated an annual loss of income of $336.8 million (US $256 million) is associated with family/friend caregiver employment disruptions.

Health information technology and specifically remote monitoring (RM) technologies can support older adults to remain in their homes [15]. Remote technologies act by notifying, in this case, a family member or friend of a possible untoward incident (ie, a fall, failure to take medications, wandering). Active RM monitoring applications require individual participation, such as pushing a button, whereas passive RM technologies such as sensors do not require any action by the individual for the system to work. Active and passive RM can increase client confidence in their self-health care and in their ability to live independently at home [16]. RM is especially helpful in tracking behaviors of older adults with cognitive decline (eg, forgetting to take medications) and allowing caregivers to intervene quickly [15]. These technologies can also benefit home-based older adults and their family/friend caregivers in the short-term by increasing communication and collaboration between and among all stakeholders [15].

We are proposing to develop and evaluate a technology-enabled RM model of home care (RMHC) to address current gaps in home care for older adults requiring the kind of complex care that includes (1) stretched health human resources, (2) partial home care services and unmet home care needs, (3) reliance on unpaid family/friend caregivers to sustain home care services with limited support to conduct this care work, (4) a chronic disease model of health care that assumes and expects client and caregiver ability for self-care, (5) lack of direct support for or involvement of family caregivers in new models of home care, and a (6) lack of innovative strategies to expand home care. RMHC is enabled by passive RM technologies (eg, sensors and cameras) and is conceptually informed by the principles of client-centered care, family as client, supported self-management, and stakeholder collaboration [4,5,17,18].

The purpose of this study is to examine the use of passive RM technologies in the home as a means of supporting older adults to safely remain in their home and avoid or delay the need for higher levels of care.

## Methods

### Study Design

This 4-year study is an unblinded pragmatic randomized controlled trial (PRCT) with two parallel arms [19-22]. PRCTs are well-suited to supporting decisions about complex interventions tested in the real world when comparing with usual care [23,24]. The objective of the study is to examine the effectiveness of the RMHC versus usual home care in maintaining the client in their place of residence and delaying or preventing admission to higher levels of care such as hospitalization or long-term care.

This study builds on the findings of previous pilot studies conducted in the provinces of New Brunswick, Alberta, Nova Scotia, and British Columbia. The primary aims of this study are to test whether (1) RM along with usual home care (the intervention) versus usual home care alone (control) allow older adults with complex care needs to remain in their home longer and delay or avoid admission to higher levels of care (eg, hospitalization and long-term care), (2) intervention is cost effective, and (3) intervention will improve the quality of life for clients and family/friend caregivers. The primary outcome for this study is the occurrence of and time to events such as terminal admission to hospital awaiting admission to long-term care and direct admission to long-term care. The secondary outcomes for this study are (1) health care costs, (2) client functional status and quality of life in the home, (3) family/friend caregiver stress, and (4) family/friend caregiver functional health status.

### Setting

The PRCT will take place in two study sites: the provinces of Nova Scotia and Ontario.

### Selection Criteria

PRCTs are meant to capture real-world situations and clients, therefore we have purposely selected broad inclusion criteria for this study (Textbox 1). To be assessed as at risk for higher levels of care, the clinical provider identifies that within the next 12 months the client is likely to be admitted to long-term care. For this research, participants must be recruited in client-caregiver dyads because the RM technology requires that older adults have a family member/friend caregiver who is willing to receive system notifications. These criteria were developed in collaboration with the regional health care partners.

Participant recruitment selection criteria.Inclusion criteria:Aged 65 years and olderAssessed as requiring complex publicly funded home careAt risk for admission to a higher level of careHave a caregiver (family member or friend or neighbor) willing to receive notifications from the remote monitoring systemWilling to have remote monitoring technology installed in their home if they are randomized to the intervention groupAble to read/write English or FrenchHave decisional capacity to consent or have a substitute decision-maker consent to participate in studyExclusion criteria:Assessed for immediate admission for higher level of careLack a family/friend caregiverNot competent to consent to participate in study or do not have a substitute decision-maker for consent

### Sample Size Calculation

The sample size calculation is based on data from one health region included in the study to estimate the study’s main outcome (time to higher levels of care). The following criteria were used to estimate sample size: the total institutionalization proportion among controls being equal to 0.41 and the proportion or the experimental subjects at 0.27 (ie, a 34% reduction compared to controls); a 10% dropout and/or lost to follow-up rate; a power of 80% and a statistical significance level of alpha=.05. This resulted in an estimate of 160 participants for the intervention group and 320 for the control group for a total target study size of 480 participants across the study sites [25,26]. We opted to increase the study power by using a 2:1 ratio of controls to intervention subjects due to the cost of the intervention.

### Recruitment

Participant enrollment in the PRCT is supported by the respective provincial regional authority. Home care recipient participants will be assessed by the case coordinator or case manager in the regional authority against the inclusion and exclusion criteria (see Textbox 1).

Consent to participate in the study will be obtained at the first meeting with the researcher and the patient and family/friend caregiver. Once consent is obtained from the participants (client and their family/friend caregiver), research staff will collect baseline data before initiating random allocation into control and intervention groups. Using block randomization, participants will receive either usual home care or RM with usual home care [27]. Randomization will occur as follows:

Twelve ping pong balls will be placed in a containerFour of each of the ping pong balls will be numbered 1 to 3Each block of 3 participants will be numbered sequentially from 1 to 3 as they appear on the master recruitment listA ping pong ball will be pulled from a container and whatever number that ball is will correspond to the numbered participant; it is that participant who will receive the interventionThe remaining 2 participants will be in the control arm (no intervention)

Allocation bias will be addressed through allocation concealment; neither the case coordinator/case manager in the home care agency or research staff will know to which group the individual will be assigned a priori.

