### Data Analysis

#### Quantitative Data

Quantitative data will be analyzed at baseline, with subsequent analysis of primary/secondary outcomes at 6 months and 12 months. Using SPSS Statistics version 25 (IBM Corp) statistical software, descriptive statistics will provide a profile of study participants including demographics, current diagnoses, length of home care before the study, and model of care (RMHC versus usual care). The provisional effect of the intervention on the primary outcome will be tested using a prospective chi-square test of independence (continuity-corrected) between the experimental and control groups (Fisher exact test). Repeated measures analysis of variance will measure mean differences between groups on continuous variables. We intend to use multivariate survival analyses methods using a relevant time dependent outcome based on the ability to accurately track the main event of interest (ie, institutionalization) [24]. We will conduct within and between province analyses on secondary outcomes. Subgroup analyses will include examining differences based on sex (male/female) in both clients and family/friend caregivers.

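### Two provincial strata are declared, but province appears neither in the written allocation steps nor in the one test specified for the primary outcome; stratifying that test is a free, modest gain

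*Protocol article*

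**What the plan says.** Three places in the protocol article bear on this.

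- **Abstract, Methods.** The design is an unblinded trial with "two parallel arms in two geographic strata (Ontario and Nova Scotia").
- **Recruitment.** Consent comes first, and then "research staff will collect baseline data before initiating random allocation into control and intervention groups". Each "block of 3 participants will be numbered sequentially from 1 to 3 as they appear on the master recruitment" list. A "ping pong ball will be pulled from a container and whatever number that ball is will correspond to the numbered participant", who receives the intervention; the other two are controls. Concealment is asserted: "neither the case coordinator/case manager in the home care agency or research staff will know to which group the individual will be assigned a priori". Province is not mentioned in these steps.
- **Data Analysis, Quantitative Data.** The intervention effect on the primary outcome, labelled provisional, is tested with a "prospective chi-square test of independence (continuity-corrected) between the experimental and control groups (Fisher exact test"). A multivariate survival analysis is also intended, with no covariates or strata named. Province enters in one sentence: "We will conduct within and between province analyses on secondary outcomes".

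**The concern.** A declared stratum should show up in how participants are allocated, in how the primary outcome is analysed, or in both. Here neither the written allocation steps nor the specified primary test uses it, and the one sentence that does use province directs it to the secondary outcomes. A reader cannot tell whether blocks are formed within each province.

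Two things follow. If both provinces share one list, their shares can differ between arms by chance, and provincial differences in admission to long-term care stay in the error of an unstratified test. If each province has its own list, an unstratified test ignores a balance that the design has already secured. A stratified test is the better choice either way.

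A smaller matter is that every block has three places and exactly one intervention place, in an unblinded trial. Concealment then depends on the block being full and fixed before the ball is drawn, and the steps do not say so in words.

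**Working it through.** **Inputs from the article (Sample Size Calculation, Recruitment).** Control proportion 0.41, intervention proportion 0.27, power 80%, alpha 0.05, 10% loss, 2:1 controls to intervention, 160 + 320 = 480, blocks of 3 with one intervention place.

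**Assumptions, because the article gives no figures by province.** Share of the larger province 50% or 70%; gap in control-arm rates between provinces 0 to 0.3.

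**1. The plan's own sample size.** With mean proportion (0.27 + 2 × 0.41)/3 = 0.3633, the two-sided formula for the smaller arm is

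n = [1.96 √(1.5 × 0.3633 × 0.6367) + 0.8416 √(0.27 × 0.73 + 0.41 × 0.59/2)]² / 0.14² = 135.4, so 136.

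The continuity correction raises this to 146, with 292 controls (438 in all). Dividing by 0.9 gives 163 and 487; multiplying by 1.1 gives 161 and 482. The stated 160 and 480 are within 3%, so the figure reproduces as a continuity-corrected two-sided test without province.

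**2. Chance imbalance if one list mixes the provinces.** With equal provinces, the SD of the between-arm difference in province share is √[0.25 × (1/160 + 1/320)] = 0.048, or 4.8 percentage points. With a 20-point gap in rates, this moves the risk difference by 0.2 × 4.8 = about 1 point (SD). The standard error of the risk difference is √(0.41 × 0.59/320 + 0.27 × 0.73/160) = 0.045, or about 4.5 points. That standard error already contains the 1 point, which is about 5% of the variance (0.97²/4.46² = 0.047).

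**3. Power with and without province.** Simulation of 20,000 trials per setting: 480 participants in blocks of 3 from one mixed list, 10% random loss, and a common odds ratio set so that the overall rates are 0.41 and 0.27.

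| Larger province | Gap | Chi-square, uncorrected | Chi-square, corrected | Cochran-Mantel-Haenszel |
|---|---|---|---|---|
| 50% | 0 | 82.4% | 79.3% | 82.3% |
| 50% | 0.1 | 83.1% | 80.3% | 83.3% |
| 50% | 0.2 | 82.7% | 79.6% | 84.0% |
| 50% | 0.3 | 82.6% | 80.0% | 85.9% |
| 70% | 0 | 82.8% | 79.9% | 82.6% |
| 70% | 0.1 | 82.6% | 79.7% | 82.8% |
| 70% | 0.2 | 82.7% | 79.7% | 83.6% |
| 70% | 0.3 | 82.5% | 79.6% | 85.1% |

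The simulation error is about √(0.83 × 0.17/20,000) = 0.3 points. Comparing like with like (neither test corrected), stratifying adds nothing at a gap of 0 and about 3 points at 0.3 (85.9 − 82.6 = 3.3; 85.1 − 82.5 = 2.6). The continuity correction alone costs about 3 points, and that loss must not be credited to stratification.

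**4. Type I error in the same settings.** Uncorrected chi-square 0.049 to 0.051; corrected 0.038 to 0.040; Cochran-Mantel-Haenszel 0.048 to 0.052. Ignoring province does not inflate it.

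**5. Predictability of a block of three.**
- Ball drawn after all three dyads are enrolled and fixed on the list: 0% of assignments are known in advance.
- Assignments released one by one: the third place is always known (1/3 of places), and the second is known when the first is intervention (1/3 × 1/3 = 1/9). Together 4/9 = 44%.

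**The case against.** **The ball draw is sound.** One might infer that a hand draw makes the randomization defective. It does not: twelve balls, four of each number, give each place a 1/3 chance. The article is silent on who draws, what is recorded and whether balls are replaced, but a condensed article may leave these to the full protocol. This objection stands in full.

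**The 44% describes a procedure the article does not state.** Consent and baseline precede allocation, three listed participants are numbered, and one ball settles the whole block. The natural reading is that the block is full before the draw, and predictability is then zero. This also stands. What remains is that the condition is not written down.

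**A single list across both provinces is an inference.** The article says that enrolment is supported by each provincial regional authority, so separate provincial lists are not excluded. That stands, so it cannot be said that stratification is absent from the allocation; it is absent only from the steps as written.

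**Province is not shut out of the primary analysis.** The chi-square test is provisional, and the intended multivariate survival model could carry province. That is fair. But the article names only one specific test for the primary outcome, that test is unstratified, and the one sentence on province concerns secondary outcomes.

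**Changing the allocation may come too late.** The article appeared in January 2020, and its Results section ends primary-outcome data collection in winter 2020, although the abstract anticipates primary completion in fall 2022. If the earlier date holds, little allocation remains to change. The analysis can still be changed.

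**Conclusion.** The point holds in a narrow form. The abstract declares provincial strata, the allocation steps do not mention province, and the only test specified for the primary outcome ignores it. A province-stratified test is better whether the lists are separate or pooled.

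The size is modest: 0 to about 3 points of power, no inflation of type I error and no change in sample size. This rests on assumed control-rate gaps of 0 to 0.3, provincial shares of 50% or 70%, a common odds ratio and one mixed list. The article gives no provincial rates to narrow that range.

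The documents do not support the stronger conclusions that the randomization is invalid, that 44% of assignments are foreseeable, or that province is used nowhere in the allocation or the primary analysis. The block-completion rule is a clarification and not a demonstrated failure of concealment.

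**What to change.** 1. Make the primary test province-stratified: Cochran-Mantel-Haenszel for the proportion, and log-rank or Cox stratified by province for time to event. State whether a continuity correction is kept, because that choice alone moves power by about 3 points.
2. Reconcile Recruitment with the abstract by stating that blocks of three are formed within province. If the lists were in fact pooled, say so; the stratified test still applies.
3. For any remaining enrolment, state that the ball is drawn only after all three dyads in the block have consented, completed baseline and been locked in order on the list.

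The cost is a few sentences. The study site is known for every participant, so no new data are needed, and the target of 480 stays as it is. Item 1 remains possible after enrolment has closed and should be fixed before the primary outcome is analysed by arm.
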